## Abstract

**Background::**

Prediabetes is an intermediate metabolic state between normoglycemia and diabetes. Without intervention, prediabetes often progresses to diabetes and prediabetes is associated with increased risk of cardiovascular disease, cancer, renal disease, and dementia. Lifestyle modification play a major role in controlling prediabetes. But lifestyle interventions are often with poor compliance and side effects of drugs are often be dislike by people. As a non-invasive therapy with no side effects, abdominal massage (AM), also called viscera massage in China, has been used to treat prediabetes and obesity-associated diseases. The gut microbiota has been recognized as an important factor in the development of metabolic diseases. Individuals with prediabetes have aberrant intestinal microbiota character. Colonic transport time and stool consistency are strongly associated with gut microbiota. Viscera massage can ease constipation by reducing colonic transport time and promoting intestinal motility. We can infer that viscera massage can modulate composition of gut microbiota affects human metabolism. So, in this trial, we will explore the mechanism of viscera massage on prediabetes from the perspective of intestinal microbiota.

**Methods and design::**

Eighty prediabetes individuals will be recruited for this study. Eighty prediabetes individuals will be divided into lifestyle intervention group and viscera massage + lifestyle intervention group by a simple random method. Each group will have 40 individuals. The manipulation of the viscera massage + lifestyle intervention group will be mainly carried out through rubbing the abdomen, kneading abdomen, vibrating abdomen, and pressing the abdomen, 30 minutes per time, once a day, with 2 days off every 5 days. Lifestyle interventions will be performed by combining pushing healthy lifestyle guidance information through Wechat application and giving face-to-face advice together daily. The lifestyle intervention group will receive healthy lifestyle intervention only. All the intervention will be conducted for 4 weeks. Weight, body mass index (BMI), waist circumference, waist-to-hip ratio, and waist-to-height ratio will be measured at the last day of every week. Triglycerides, total cholesterol, low-density lipoprotein cholesterol, high-density lipoprotein cholesterol, fasting blood-glucose, 2-hour post-meal blood glucose (2hPG) and glycosylated hemoglobin, fasting insulin and insulin resistance index will be tested at the first day and last day of the intervention course. The fecal samples of subjects will be gathered at the first day and last day of the intervention course and will be performed 16S rRNA gene sequencing and metagenomic detection. Finally, the effect and potential mechanism of viscera massage on prediabetes will be discussed in combination with all the results.

**Discussion::**

The results of this study will be used to verify the effect of AM on prediabetes and explore the mechanism of AM on prediabetes from the perspective of gut microbiota.

## Introduction

1

Prediabetes is an intermediate metabolic state between normoglycemia and diabetes, including impaired fasting glucose (IFG), impaired glucose tolerance (IGT), and the mixed-status (IFG+IGT).^[1]^ Approximately 5–10% of people with prediabetes will become diabetic each year, and up to 70% of individuals with prediabetes will eventually develop diabetes in their lifetime.^[2]^ The U.S. National Health and Nutrition Examination Survey suggests that 35% of US adults over 20 years of age and 50% of those over 65 had prediabetes in 2005 to 2008 based on fasting glucose or glycosylated hemoglobin (HbA1c) levels.^[3]^ Within the Asian region, the prevalence of prediabetes among adults reaches 50% in China, with Indians 18.9%, and Malays 22.6% respectively.^[4,5]^ Prediabetes is more prevalent than diabetes^[6]^ and pre-diabetes is more prevalent in women (21.9%) and urban dwellers (21.5%).^[4]^ Without intervention, prediabetes often progresses to diabetes and prediabetes is associated with increased risk of cardiovascular disease, cancer, renal disease, and dementia.^[7]^ People with prediabetes may have concomitant damage to end organs, such as eyes, kidneys, blood vessels, and the heart that are traditionally considered to be complications of diabetes.^[3]^ Lifestyle modification, including weight loss, dietary changes, and increased physical activity, play a major role in controlling prediabetes. Significant evidence also supports the effectiveness of a combination of lifestyle modification and pharmacologic therapy, such as metformin, in delaying the onset of diabetes.^[4]^ But lifestyle interventions are often challenging and with poor compliance.^[8]^ People are always afraid of the side effects of drugs. As a non-invasive treatment with no side effects, AM, also called viscera massage in China, has been used to treat prediabetes as well as the associated overweight and obesity. Mechanical AM and manual AM had been used to reduce cellulite,^[9]^ thigh and infraumbilical circumference,^[9]^ arm and post-partum abdominal, and flank subcutaneous fat deposits,^[10]^ improve skin laxity,^[10]^ and serum lipids.^[11]^ Manual AM also can enhance the effectivity of cryolipolysis treatment.^[12]^ As prediabetic individuals are often overweight or obese,^[13]^ AM has been used to manage prediabetes, and can significantly reduce the levels of fasting blood-glucose (FBG) and 2 hours postprandial blood glucose (2hPBG) in patients with prediabetes, with the decrease of 2hPBG more significant.^[14]^ In order to uncover the underlying mechanism of AM, several animal experiments had been carried out. AM can alleviate glucose and lipid metabolism disorder by regulating of AMPK/Glut4 signaling chain, the gene transcription and protein expression of Nuclear factor kappa beta and interleukin-6 in skeletal muscle,^[15,16]^ gut microbiota and bile acid metabolism^[17]^ in T2DM rats. Prediabetes is intertwined with the increasing incidence of metabolic syndrome and obesity. Prediabetes and T2DM has similar pathophysiology. However, there are few clinical studies and mechanism studies specially on prediabetes.

The gut microbiota has been recognized as an important factor in the development of metabolic diseases such as prediabetes, T2DM, and obesity, and is considered an endocrine organ involved in the maintenance of energy homeostasis and host immunity.^[18]^ The intestinal microbiota species may interact with host metabolism through metabolite-mediated stimulation of enteric hormones and other systems outside of the gastrointestinal tract, such as the endocannabinoid system. Individuals with prediabetes have aberrant intestinal microbiota characterized by a decreased abundance of the genus Clostridium and the decreased abundance of bacterium *A. muciniphila*.^[19]^ Based on previous studies and the important role of gut microbiota in metabolism, the proposed clinical trial will determine the possible effects of AM on prediabetes by evaluating the FBG, 2-hour post-meal blood glucose (2hPG), HbA1c, fasting insulin, insulin resistance index (HOMA-IR), blood lipid, BMI, waist-to-hip ratio, and waist-to-height ratio (WHtR), and will explore the mechanism of viscera massage on prediabetes from the perspective of intestinal microbiota.

## Methods and design

2

### Objectives

2.1

To determine the possible effects of viscera massage on prediabetes and to investigate the role of gut microbiota in improving prediabetes.

### Setting

2.2

The patients will be recruited from the Department of tuina, Affiliated Hospital of Changchun University of Chinese Medicine, Hongqi First Community Health Service Center, Chaoyang District and Hongqi Second Community Health Service Center, Chaoyang District. Patients participating in the trial will be screened strictly according to the diagnostic criteria, inclusion criteria, and exclusion criteria. The sample size estimation will be based on the clinical calculation formula employed for small sample size. The estimate sample size is (n = 36). So, the therapeutic effect could be evaluated by the sample size of >36 in each group. In this study, 80 individuals will be recruited by simple random method and divided into two groups, 40 individuals in each group.

The researcher of the project will record the subject's basic information (such as date of birth, age, sex, and address) and answer questions patient involved in the trial. After completed the recruitment, individuals involved will be assigned a trial study serial number, also the patient's unique identification number, according to the order of enrollment, until the total numbers (n = 80) are all allocated. The odd-numbered individual was divided into the lifestyle intervention group, with the even-numbered individual the viscera massage + lifestyle intervention group. After clinical evaluation, blood and stool sampling, viscera massage therapy will be adopted.

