### Stripping and shedding criteria

2.9

After enrollment, patients who meet one of the following criteria will be terminated from the trial. The stripping criteria: those who might fail to meet the inclusion criteria and have entered the study. Those who might to follow the prescribed treatment or incomplete data affecting the efficacy evaluation and safety evaluation. Those who might have used the different therapeutic methods prohibited by this protocol. Those who might change the treatment plan midway by themselves. The shedding criteria: the subjects with poor compliance and self-withdrawal during the course of treatment. Those who might display serious adverse events or in those in which complications might occur. Those who will be unable to continue the treatment for various reasons.

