#### Statistical method

2.11.5

SPSS23.0 statistical software will be used for statistical analysis for all the data generated. Chi-square test will be used for enumeration data. Paired *t* test will be used for the comparison of measurement data before and after the treatment. One-way analysis of variance (ANOVA) will be used for comparison between the groups, with *P* < .05 as difference and *P* < .01 as significant difference.

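### Forty per group leaves room for only three losses against the stated need for more than 36, and the post-enrolment removal rules mean that size is not secured

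*Protocol article*

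**What the plan says.** Section 2.2 (Setting) of the protocol article describes the calculation in one sentence: "The sample size estimation will be based on the clinical calculation formula employed for small sample size". It gives the result as "The estimate sample size is (n = 36"), and then concludes: "So, the therapeutic effect could be evaluated by the sample size of >36 in each group". The planned enrolment follows: "80 individuals will be recruited by simple random method and divided into two groups, 40 individuals in each group". No allowance for losses is mentioned.

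Three other sections bear on who is left to analyse:

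- **Section 2.9 (Stripping and shedding criteria)** terminates enrolled people who meet any of a list of criteria. These include incomplete data, unauthorised change of treatment, inability to continue, and "the subjects with poor compliance and self-withdrawal during the course of treatment".
- **Section 2.7 (Exclusion criteria)** also lists withdrawal, refusal of treatment and unwillingness to follow the lifestyle programme during treatment, although these can only occur after enrolment.
- **Section 2.8 (Termination of the standard)** lets some people with interrupted treatment enter the efficacy statistics, in wording whose threshold is hard to read. Section 2.3 adds that the consent form asks whether data may be used after a person opts out.

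For the comparison between arms, section 2.11.5 says: "One-way analysis of variance (ANOVA) will be used for comparison between the groups".

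**The concern.** The article sets a minimum number per group, enrols only slightly more, and then lists broad grounds for taking people out after allocation. Its introduction observes that "lifestyle interventions are often challenging and with poor compliance", and both arms receive a lifestyle intervention.

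Two things are at stake. The first is size: if removals under section 2.9 also leave the analysis, the groups compared may fall below the number the article says it needs. The second is validity: compliance is observed after allocation and can be affected by the arm. One arm has treatment-day massage sessions of 30 minutes on top of the lifestyle advice, so the people who comply poorly need not be of the same kind, or as many, in the two arms. Comparing only those who remain is then no longer a comparison of the groups as allocated. Of the two, the second would matter even if the numbers held up.

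**Working it through.** **The stated figure.** The 36 cannot be reproduced, because the article names no formula, outcome, effect, standard deviation or power. It is taken below as the article uses it, per group.

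**Margin.** Inputs from section 2.2: 40 enrolled per group, more than 36 needed, so at least 37.

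- Tolerated losses per arm: 40 − 37 = 3, and 3/40 = 7.5%.
- If exactly 36 is accepted: 40 − 36 = 4, and 4/40 = 10%.
- Equivalently 36/(1 − 0.10) = 40, so 40 is what a 10% allowance on 36 would give. A 10% loss then leaves 40 × 0.90 = 36, which meets 36 but not more than 36.

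**Chance of keeping the stated size.** The article gives no loss rate, so the rates below are assumptions shown as a range. With loss probability q, independent between people and equal in the two arms, the number lost per arm is binomial(40, q). The chance that both arms keep at least 37 is P(at most 3 lost)². For at least 36 it is P(at most 4 lost)².

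| Assumed loss | Expected left per arm | One arm keeps ≥37 | Both keep ≥37 | One arm keeps ≥36 | Both keep ≥36 |
|---|---|---|---|---|---|
| 5% | 38 | 0.862 | 74% | 0.952 | 91% |
| 7.5% | 37 | 0.647 | 42% | 0.822 | 68% |
| 10% | 36 | 0.423 | 18% | 0.629 | 40% |
| 15% | 34 | 0.130 | 1.7% | 0.263 | 6.9% |
| 20% | 32 | 0.028 | 0.1% | 0.076 | 0.6% |

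For example, at 10% loss: 0.423² = 0.179 and 0.629² = 0.396.

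**What the size delivers.** With two groups, one-way ANOVA is the two-sided t test. The standardised difference d detectable with 80% power at two-sided 5% solves the noncentral t power equation with 2n − 2 degrees of freedom and noncentrality d√(n/2):

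- n = 40 per group: d = 0.634
- n = 36: d = 0.670
- n = 32 (20% loss): d = 0.711

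The normal approximation at n = 40, (1.960 + 0.842) × √(2/40) = 0.626, agrees closely. For a difference of 0.5 SD, power is 60% at 40 per group and 55% at 36.

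So a few losses change precision only modestly (0.63 to 0.67 SD between 40 and 36). The numerical shortfall is against the article's own threshold and is not a collapse of power.

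**Who is analysed.** Read together, the sections do not settle it. Section 2.9 ends participation for poor compliance or incomplete data and does not expressly say what happens to the data already collected. Section 2.8 admits some early leavers to the efficacy statistics. Section 2.3 foresees use of data after opting out. Section 2.7 treats events during treatment as exclusions. A person who stops midway could be counted or not, depending on which section is followed.

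**The case against.** The strongest reply is that nothing here shows the trial will fall short. No loss rate is stated, the course lasts only four weeks with daily face-to-face advice, and participants must agree to the intervention beforehand. The introduction's remark on compliance is general background without a rate. At 5% loss both arms keep at least 37 with probability 74%, or 91% if 36 is enough. Forty is also exactly 36 with a 10% allowance, even though the article does not say so. Sections 2.3 and 2.8 suggest that leavers' data may be kept. All of this stands, and it rules out calling a shortfall likely as a matter of record.

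A reader might go further and infer that 36 or 40 is the wrong size, or that the therapeutic effect cannot be evaluated at all. The article does not support that. The missing outcome, effect, standard deviation and power may be in a fuller protocol, and their absence from a condensed article is not an error. A reader might also take 36 as a total of both groups, but the sentence that follows it says the figure is per group.

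What the reply does not remove is that the retained number depends on removal rules that conflict, and that at least one of them selects on compliance.

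**Conclusion.** The concern holds in a limited form. Against its own requirement of more than 36 per group, the plan has a margin of 3 losses per arm (7.5%) and states no allowance. If section 2.9 governs the analysis, whether that size survives depends heavily on the loss rate. Both arms meet it with probability 74%, 18% and 1.7% at 5%, 10% and 15% loss, or 91%, 40% and 6.9% if exactly 36 is accepted. These figures assume independent losses at the same rate in both arms, and the rates themselves are assumptions. If leavers' data are used, as sections 2.3 and 2.8 suggest for some, the shortfall shrinks or disappears.

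The stated size is therefore not secured, which is weaker than saying it will be missed. The more important consequence is that removal by compliance can bias the comparison between arms, whatever number remains. The direction and size of that bias cannot be derived from the document.

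**What to change.** No extra patients are needed.

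1. Reconcile sections 2.7, 2.8 and 2.9, together with the consent wording in 2.3, so that stopping treatment or complying poorly does not by itself remove a person from the analysis. This concerns the analysis only. When a participant should stop treatment is a clinical matter and is left as it is.
2. Analyse all 80 in their allocated arm. Seek end-of-treatment measurements from those who stop, within their consent, and state a missing-data method for the rest.
3. Limit the sentence in section 2.2 to what the size delivers, for the outcome on which the calculation was made. For example: 40 per group gives 80% power (two-sided 5%) for a difference of about 0.63 SD, and 32 evaluable per group for about 0.71 SD.

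The cost is some follow-up of people who stop treatment, slightly more analysis work, and a stated capability that reads less favourably than the present one.

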## Advantages and limitations of proposed study

5

The study will be safe and reliable. We will perform abdominal massage and lifestyle modifications on patients with prediabetes. The 2 types of intervention means are almost no risk.

After treatment, the individuals will be assessed by physical examination (weight, BMI, WC, WHR, WHtR), chemical examination (triglycerides, total cholesterol, low-density lipoprotein cholesterol, high-density lipoprotein cholesterol, FBG, 2hPG and HbA1c, fasting insulin, and HOMA-IR), and 16S rRNA gene sequencing and metagenomic detection, the above of which are harmless to people.

The advantages of this study will be its safety, reliability, practicability. In this clinical trial, the rights and interests of the subjects will be fully guaranteed. The limitation is the lack of double-blind control and completely-randomized design.

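### The abstract describes simple random allocation, but the operating rule is odd/even alternation by enrolment order, which anyone holding the running count can foresee

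*Protocol article*

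**What the plan says.** The abstract (Methods and design) states: "Eighty prediabetes individuals will be divided into lifestyle intervention group and viscera massage + lifestyle intervention group by a simple random method". It adds a fixed split: "Each group will have 40 individuals".

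Section 2.2 (Setting) uses the same term, there attached to recruitment: "80 individuals will be recruited by simple random method and divided into two groups, 40 individuals in each group". It then describes the mechanism. On timing: "After completed the recruitment, individuals involved will be assigned a trial study serial number". On sequence, numbers are given "according to the order of enrollment, until the total numbers (n = 80) are all allocated". On arm: "The odd-numbered individual was divided into the lifestyle intervention group, with the even-numbered individual the viscera massage + lifestyle intervention group".

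Section 5 (Advantages and limitations) says: "The limitation is the lack of double-blind control and completely-randomized design".

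**The concern.** The article does more than leave sequence generation to a fuller document. It fixes a deterministic rule and gives it a random label. The arm depends only on the parity of the enrolment number, so the order in which people are entered decides who receives massage.

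This matters because some entry conditions in section 2.6 need judgement: previous failure of diet and exercise efforts, and willingness to accept massage. A recruiter who can foresee the next arm may, knowingly or not, bring forward, defer or decline a candidate. Both arms receive a lifestyle intervention that relies on the participant's effort, so motivation could plausibly affect weight, waist and glucose. A difference in motivation between arms at entry would be mixed with the effect of massage. The trial is not double-blind, so blinding does not offset this.

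**Working it through.** **1. The statements side by side.**

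| Place | What it implies for allocation |
|---|---|
| Abstract, Methods and design | Division into groups is random; 40 per group |
| Section 2.2, first paragraph | Same term, attached to recruitment; 40 per group |
| Section 2.2, second paragraph | Number follows enrolment order; odd = lifestyle only, even = massage + lifestyle |
| Section 5 | Not double-blind, not completely randomised |

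The first and third rows cannot both describe the allocation. The third is the only one specific enough to carry out, and following it exactly involves no chance.

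**2. How foreseeable the next arm is.** This is the share of the 80 assignments that can be guessed correctly by someone who sees all earlier ones. The figures for restricted lists come from 20,000 simulated lists each.

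| Scheme | Share guessable |
|---|---|
| Odd/even alternation | 80/80 = 100% |
| Permuted blocks of 4 | about 71% |
| Permuted blocks of 8 | about 67% |
| One random list fixed at 40/40 | about 56% |
| Unrestricted simple randomisation | 50% |

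The 100% applies to a person holding the running count. With a concealed list, the next assignment is not disclosed.

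**3. How large a bias could be.** The document gives nothing from which to estimate this, so the following inputs are assumptions: no true effect; outcome SD 1; 40 per arm (from the protocol); two-sided t test at 5%. For a fraction p of massage places the recruiter takes the candidate who looks better of two, and the other candidate is not entered in the lifestyle arm. The recruiter's judgement correlates ρ with outcome.

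The expected larger value of two independent standard normal draws is 1/√π = 0.564, so

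head start = p × ρ × 0.564 SD.

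For example, p = 0.25 and ρ = 1 gives 0.25 × 0.564 = 0.14 SD. With p = 0.50 and ρ = 0.5 it is 0.50 × 0.5 × 0.564 = 0.14 SD. Rejection rates are from 100,000 simulated null trials per cell. With p = 0 the rate was 5.0% or just under, as it should be.

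| p | ρ = 1 | ρ = 0.5 | ρ = 0.3 |
|---|---|---|---|
| 10% | 0.06 SD, 5.7% | 0.03 SD, 5.1% | 0.02 SD, 5.1% |
| 25% | 0.14 SD, 9.7% | 0.07 SD, 6.2% | 0.04 SD, 5.4% |
| 50% | 0.28 SD, 25% | 0.14 SD, 9.9% | 0.08 SD, 6.6% |

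The ρ = 1 column assumes the recruiter foresees each person's outcome perfectly, so it is an upper bound for this kind of selection and not a forecast.

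**4. The 40/40 split.** Unrestricted simple randomisation of 80 people gives exactly 40/40 with probability C(80,40)/2^80 = 0.089. The fixed split therefore does not fit a literal reading of simple randomisation. It says nothing about bias, because a restricted random list also gives 40/40.

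**The case against.** **Foreknowledge is not certain for every recruiter.** There are three recruiting sites. If they share one number sequence, a recruiter needs the count from all three, and the document does not say it is available. The timing phrase could also mean that numbers are issued only once all 80 are recruited. This stands as a limit: a reader might infer that the next arm is always known to everyone, and the text does not support that. It does not remove the problem. The number still follows enrolment order, so whoever holds the count can foresee the arm, and no concealment is described.

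**The weakness is partly disclosed.** Section 5 does name the lack of a completely randomised design, and the authors should have credit for it. But it does not withdraw the abstract's wording or mention predictability.

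**The random term in section 2.2 describes recruitment.** Grammatically it does. The abstract, however, applies it plainly to division into groups.

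**Baseline data can help.** Glucose, HbA1c, insulin, lipids and body measures are taken before treatment, so imbalance in them can be seen and adjusted for. This stands, and it would be too strong to say that no baseline difference could be separated from the massage effect. Unmeasured motivation remains out of reach.

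**Nothing shows that selection will occur.** This is also true. The manipulation rates and the two-candidate queue are assumptions. Poor compliance should not be counted among the judged entry criteria either: it appears in sections 2.8 and 2.9 as a ground for termination or shedding, not among the inclusion criteria in section 2.6.

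**Conclusion.** The point holds. The abstract calls the allocation random, section 2.2 specifies alternation by enrolment order, and nothing elsewhere in the document reconciles the two. Carried out as written, the trial is quasi-randomised and its allocation can be foreseen by anyone with the running count.

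That conclusion rests on the text alone. The size of any resulting bias does not. Over the assumptions shown, it runs from negligible (0.02 SD, about 5% rejection) to serious (0.28 SD, about 25%), and the serious end needs both frequent selection and perfect foresight of outcome. A reader might infer that the trial's type I error is in fact 10% or 25%, or that the exact 40/40 split itself shows bias. The documents support neither.

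**What to change.** - **Allocation rule (section 2.2).** Replace the odd/even rule with a computer-generated 1:1 random sequence prepared by someone not involved in recruitment. Keep it concealed, and release each assignment only after consent, eligibility and baseline sampling are complete. Restricted randomisation can keep the 40/40 split; block sizes and stratification by centre are optional.
- **Wording.** Make the abstract, section 2.2 and section 5 describe the same method.
- **Participants already allocated by parity.** Section 4 gives a start in December 2021 and expected completion of recruitment by February 2023, so some or all allocation may already be done. For those participants, remove the simple random wording, describe the allocation as quasi-randomised (alternation), and limit the conclusions accordingly.

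**Cost.** A short amendment and one generated list, with no extra participants or visits and no change in the required sample size. The downside of switching mid-trial is that the truly randomised subset will be smaller than 80. If allocation is complete, only the relabelling and the more cautious conclusions remain.

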### Participants and recruitment

2.3

The recruitment posters will be displayed in the hospitals and community. And the forward recruitment information will be posted on WeChat to recruit the potential participants for this study. The participants will be explained in detail about the potential benefits and services to be provided and the risks associated with participating in the study, including the possible associated adverse clinical outcomes with viscera massage therapy. An informed consent will be signed after reading carefully by each participant prior to the participation. On the consent form, participants will also be asked whether they agree to use their data even if they opt out of the trial. The participants will also be required to obtain permission for the research team to share relevant information with staff from the participating hospitals or regulatory agencies. The participants will receive 4 different courses of viscera massage therapy. The personal information of all the participants will be kept confidential by the researchers and used only for this study. The patients must properly understand and sign informed consent. The FBG and 2hPG will be used to potentially determine whether participants meet the inclusion criteria. Patients who met the criteria will be included in the study (Fig. 1).

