#### Blood sample

2.11.2

Blood samples will be taken from each participant twice—one before the first treatment, and the other following the last treatment. Measurements will include triglycerides, total cholesterol, low-density lipoprotein cholesterol, and high-density lipoprotein cholesterol, FBG, 2hPG, and HbA1c, fasting insulin and HOMA-IR.

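### As written, baseline can be measured and ineligible people removed after an openly known odd/even assignment, and the timing of the eligibility glucose tests is unclear

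*Protocol article*

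**What the plan says.** **Allocation (section 2.2).** Patients are screened against the criteria. Serial numbers are then given "according to the order of enrollment, until the total numbers (n = 80) are all allocated", and the number decides the arm: "The odd-numbered individual was divided into the lifestyle intervention group, with the even-numbered individual the viscera massage + lifestyle intervention group". The next sentence reads "After clinical evaluation, blood and stool sampling, viscera massage therapy will be adopted".

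**Timing of baseline.** The documents differ by type of measure:
- Body measures: section 2.11.1 has the study nurse take them on day one of the intervention and at each week's end.
- Blood: the abstract says the tests "will be tested at the first day and last day of the intervention course". Section 2.11.2 describes two samples per participant, "one before the first treatment, and the other following the last treatment", and includes FBG and 2hPG.
- Stool: the abstract says "The fecal samples of subjects will be gathered at the first day and last day of the intervention course". Section 2.11.3 says only that samples come before and after the intervention.

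**Eligibility.** Section 2.3 states "The FBG and 2hPG will be used to potentially determine whether participants meet the inclusion criteria" and that those who meet the criteria are then included.

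**Removal after entry.** Section 2.9 applies after enrollment and covers "those who might fail to meet the inclusion criteria and have entered the study".

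**Analysis and blinding.** Section 2.11.5 uses paired t tests before and after treatment and one-way ANOVA between groups. Section 5 concedes that the trial is neither double-blind nor completely randomized.

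**The concern.** Baseline is one side of every before-after comparison, so it should be recorded when neither the participant nor the measurer can know the arm. Here the arm follows from a visible serial number, and at least the body measures are scheduled once the intervention has begun. A nurse who knows the arm can, without intending to, read a tape differently. A participant who knows it may act differently before a first-day visit, or may not attend.

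Removing people for ineligibility after the arm is known is a second route to bias. Whether a borderline case is re-examined, and whether that person is then dropped, can depend on the arm. The groups compared would then no longer be the groups assigned.

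The unclear timing of the eligibility FBG and 2hPG bears on both routes. It determines whether a second pre-treatment glucose value exists on which someone already allocated could be judged ineligible.

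**Working it through.** **1. Order of steps.** Section 2.2 runs: screening, serial number by order of enrollment, arm by odd or even number, then a sentence that puts evaluation and sampling before massage. That sentence does not itself say that sampling follows allocation. The later timing comes from elsewhere:

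| Baseline measure | Where timed | Relation to allocation |
|---|---|---|
| Weight, BMI, WC, WHR, WHtR | 2.11.1: first day of intervention | after, as written |
| Blood | abstract: first day; 2.11.2: before first treatment | after by the abstract; open by 2.11.2 |
| Stool | abstract: first day; 2.11.3: before the intervention | after by the abstract; open by 2.11.3 |

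The first day of an assigned intervention comes after assignment. The methods text therefore supports the point firmly for body measures. For blood and stool it holds only if the abstract is taken literally.

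**2. Exposed outcomes.** WC is taped, WHR = WC/hip and WHtR = WC/height. Three of the five body outcomes therefore depend on a tape. Weight on an electronic scale and laboratory values leave less room for the measurer.

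**3. Effect of a shifted baseline.** The between-arm difference in change is (F1 − B1) − (F0 − B0), with F the final and B the baseline mean. If B1 is read δ too high, this becomes the true difference − δ, and the paired change in arm 1 also moves by −δ. With δ = 1 cm of waist, both move by 1 cm. This is arithmetic, not an estimate of how large δ is. If the ANOVA is run on final values only, the between-group test escapes this error but the paired tests do not.

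**4. Eligibility draw.** Two readings are possible:
- The pre-treatment draw of 2.11.2 decides eligibility. By 2.3 it then precedes inclusion, hence the serial number, and cannot be a first-day draw as in the abstract.
- A separate screening test decides eligibility. The two samples of 2.11.2 are then outcome samples only, and a third draw goes unmentioned.

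Either is tenable, and the text does not choose.

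**5. Selective removal (illustration only).** The documents give no removal rate. Assumptions: 40 per arm, no true effect, standardized normal values, baseline–final correlation ρ of 0.5 or 0.7, the k lowest baselines removed from one arm only, two-sided 5% t test, 20,000 simulated trials.

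| k removed | Baseline shift (SD) | Error rate, change scores | Error rate, final values |
|---|---|---|---|
| 0 | about 0 | 4.8–4.9% | 5.2–5.3% |
| 2 | 0.10 | 5.4–6.0% | 6.2–6.5% |
| 4 | 0.19 | 6.2–7.2% | 7.4–9.4% |
| 6 | 0.27 | 7.3–9.2% | 9.0–13.6% |

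As a check, the bias in change should be about −(1 − ρ) × shift. For k = 4 and ρ = 0.5 this is −0.5 × 0.188 = −0.094, against −0.092 simulated. For ρ = 0.7 it is −0.3 × 0.186 = −0.056, against −0.057. The bias appears as a fall in the arm that lost its lowest values. One-sided removal of extremes is an unfavourable case; removals made equally in both arms would do less harm.

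The protocol's sample size of 36 plays no part in this point.

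**The case against.** The strongest reply is that the article is condensed and nothing in it forces sampling to follow allocation. The sentence in 2.2 fixes sampling before massage only. Sections 2.11.2 and 2.11.3 allow blood and stool to be taken before allocation, and the flow chart, which is not shown, may settle the order. This stands for blood and stool. It does not answer 2.11.1, which sets a first-day body baseline in the methods text, and the abstract still needs to be reconciled with 2.11.2 and 2.11.3.

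A reader might infer that the single pre-treatment draw also carries the eligibility tests, so that eligibility is read only after allocation. The documents do not support this. Sections 2.2 and 2.3 put screening before inclusion, and 2.11.2 sits among the evaluation indicators and may count outcome samples only. The inference also defeats itself, because a draw that decides inclusion would precede allocation.

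It is also fair to say that HbA1c or scale weight can hardly move because the arm became known shortly beforehand, that 2.9 does not say who decides removals or tie them to first-day glucose, and that no section says when the nurse or participant learns the arm. These points limit the likely size of the bias. They do not close either route, since the odd/even rule is open and blinding is disclaimed.

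Finally, alternation is the larger defect, and Section 5 concedes incomplete randomization. That is correct. Yet a concealed sequence alone would leave the first-day baseline and the post-entry removals where they are, so this point needs its own correction.

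**Conclusion.** The concern holds in a limited form. As written, the body baseline follows an open assignment, and so do blood and stool if the abstract is taken literally. The tape-based WC, WHR and WHtR are the most exposed. Section 2.9 allows people to be removed as ineligible once the arm is known. The source of the eligibility FBG and 2hPG is left unclear.

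A reader might go further and conclude that every outcome has a post-allocation baseline. The documents do not support that, because 2.11.2 and 2.11.3 leave blood and stool open.

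The size cannot be estimated from the documents. A baseline shift passes one for one into change. In the unfavourable illustration, two to six selective removals from one arm of 40 raise a nominal 5% error rate to between 5.4% and 13.6%, depending on the number removed, the correlation and the analysis. These figures show direction and scale and are not a forecast. The correction is worthwhile because it is cheap and the trial is open-label with before-after tests.

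**What to change.** - **Sections 2.2, 2.11.1 and 2.11.2, with the abstract and 2.11.3 aligned:** state that eligibility results are reviewed, and that all baseline body, blood and stool measures are complete, before the arm is assigned.
- **Section 2.2:** release the arm from a concealed random sequence. Giving the serial number later while keeping odd/even alternation would not be enough, because staff could still predict the next arm.
- **Sections 2.3 and 2.11.2:** say whether the FBG and 2hPG used for eligibility come from a screening draw separate from the two outcome draws, or from the pre-treatment outcome draw.
- **Section 2.9:** limit removal for failed inclusion criteria to people shown to be ineligible on data collected before allocation, and keep all other assigned participants in the main analysis. This concerns who is analysed, not when treatment stops.

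The cost is a reordering of existing steps and a short wait between consent and allocation while laboratory results return.
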